## Abstract

Poor intervertebral disc (IVD) health is associated with low back pain (LBP). This 12-week parallel randomised controlled trial will evaluate the efficacy of a progressive interval running programme on IVD health and other clinical outcomes in adults with chronic LBP. Participants will be randomised to either a digitally delivered progressive interval running programme or waitlist control. Participants randomised to the running programme will receive three individually tailored 30 min community-based sessions per week over 12 weeks. The waitlist control will undergo no formal intervention. All participants will be assessed at baseline, 6 and 12 weeks. Primary outcomes are IVD health (lumbar IVD T2 via MRI), average LBP intensity over the prior week (100-point visual analogue scale) and disability (Oswestry Disability Index). Secondary outcomes include a range of clinical measures. All outcomes will be analysed using linear mixed models. This study has received ethical approval from the Deakin University Human Research Ethics Committee (ID: 2022-162). All participants will provide informed written consent before participation. Regardless of the results, the findings of this study will be disseminated, and anonymised data will be shared via an online repository. This will be the first study to evaluate whether a progressive interval running programme can improve IVD health in adults with chronic LBP. Identifying conservative options to improve IVD health in this susceptible population group has the potential to markedly reduce the burden of disease. This study was registered via the Australian New Zealand Clinical Trials Registry on 29 September 2022 (ACTRN12622001276741).

WHAT IS ALREADY KNOWN ON THIS TOPICExercise training is known to improve a range of health-related outcomes (eg, pain intensity and disability) in adults with chronic low back pain.WHAT THIS STUDY ADDSThis randomised controlled trial will be the first to examine the safety and efficacy of a progressive interval running programme on intervertebral disc (IVD) health.HOW THIS STUDY MIGHT AFFECT RESEARCH, PRACTICE OR POLICYThis study represents a critical step towards identifying a conservative treatment capable of improving IVD health in this susceptible population group.

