### Eligibility criteria

We will recruit a sample of 40 adults (18–45 years) with non-specific (no known specific pathology) chronic (>12 weeks) LBP (pain located between the costal margin and above the inferior gluteal folds, with or without leg pain and experienced on most days in an average week). Exclusion criteria will consist of: (a) history of spinal surgery, spine trauma (eg, fracture or car accident), cauda equina symptoms, known structural scoliosis requiring surgical consultation, symptomatic radiculopathy (diagnosed via medical professional or leg pain greater than back pain), inflammatory spondyloarthropathies or non-musculoskeletal causes of LBP (eg, infection), (b) inability to communicate in English, (c) pregnancy, lactating or less than 1-year postnatal, (d) current or prior elite athletes (eg, member of Australian Institute of Sport, State Institutes or Academies of Sport or the national squad of any sport),^19^ (e) any absolute contraindications for MRI, (f) any absolute contraindications for exercise training, (g) participation in running or sport that involves running in the last 3 months (>1 session per month), (h) having experienced a lower limb injury in the last 6 weeks, (i) deemed higher risk of adverse event due to physical activity per the Adult Pre-Exercise Screening System^20^ and (j) unable to access a smartphone with a cellular internet connection.

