The exercise programme will consist of short running intervals interspersed with rest periods of walking (table 1). This interval-based training is an effective way to increase running capacity in untrained novice runners^21^ and is recommended following hip and lower limb injuries to safely return to running.^22–24^ Participants enter the interval training programme at stage 1, 2 or 3 as determined by a 2 min running tolerance test at the initial physical assessment. During this run test, participants will be instructed to run at a slow to moderate pace for as long as they are comfortable, up to a maximum of 2 min. Participants who can complete the slow run comfortably for: (a) 0–44 s will start at stage 1 of the programme; (b) 45–89 s will start at stage 2 of the programme; and (c) 90–120 s will start at stage 3 of the programme. Participants may choose their starting point (stage 1, 2 or 3) in consultation with the accredited exercise physiologist, irrespective of the test results. At each stage, participants can self-select their chosen number of repeats to complete based on their overall perceptions of exertion, breathlessness and pain intensity. For example, at stage 2, participants can select to complete between 6 and 10 repeats of 30 s running. This approach accounts for the daily fluctuations in pain intensity observed in up to 35% of individuals with CLBP^25^ while promoting self-efficacy through autonomy and shared decision-making.^26^ Once participants complete the upper repeat range each week, they progress to the next stage. To reduce the risk of injury due to the rate of progression, participants can only increase one stage per week and must complete at least two sessions per week before progressing to the following stage.^22^ The increase in average running time per week (table 1) is greater over the first 6 weeks and reduces throughout the programme. This is due to a conservatively chosen starting point to facilitate confidence with running, facilitate familiarity with sensations associated with muscle fatigue and reduce the interference of possible fatigue-related pain interpreted as injury pain. For example, the graded exposure to running commences at 1.5 min total running time per session at stage 1, progressing by 20%–100% over the first 6 weeks before levelling off to increases of approximately 10%–15% after that. Importantly, in novice runners, there is no difference in the prevalence of running-related injuries between training programmes that adhere to a strict 10% weekly increase and those that include greater weekly progressions of up to 50%.^27^ If participants reach the final stage before the end of the intervention, they will stay in this stage for the remaining weeks. Throughout the intervention, participants will be advised to run at a slow to moderate pace (maximum of 10 km per hour or 6 min per km), which corresponds with velocities thought to have a positive stimulus on the IVD.^12^ In collaboration with the accredited exercise physiologist, participants can regress to an earlier stage of the interval programme if deemed necessary (eg, significantly increased LBP, other injuries/soreness, following periods of poor adherence).

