#### Feasibility

The following domains of feasibility will be documented throughout the study by members of the research team: recruitment ((1) enrolled participants compared with total screened potential participants, (2) reasons for ineligibility or declined participation, (3) enrolment timeline, (4) efficacy of recruitment pathways), attrition ((1) number of participants available for follow-up, (2) reasons for loss to follow-up), adherence ((1) overall training session attendance, (2) within-session training load completed), data collection ((1) missing data, (2) reasons for missing data), safety ((1) number of adverse events, (2) severity of adverse events), acceptability ((1) system usability survey). For feasibility purposes, additional pain intensity (visual analogue scale) measurements will be conducted at fortnightly intervals during the video consultation for the intervention group only.

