#### Adverse events

Participants will be instructed to inform the research team immediately should any adverse events occur. Moreover, participants allocated to exercise training will be asked about adverse events during a fortnightly video consultation (Zoom Video Communications, California, USA) with a study team member. Serious adverse events will be defined as any untoward medical occurrence that results in death, is life-threatening or requires hospitalisation. Non-serious adverse events will be defined as any other untoward medical occurrence. Adverse events will be classified as treatment-related if they are definitely or probably related to the exercise training intervention.

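### The closed serious adverse event definition has no disability criterion, so a lasting disabling injury managed without admission would be reported as non-serious

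*Protocol article*

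**What the plan says.** The Adverse events section of the protocol article defines two classes. The first is: "Serious adverse events will be defined as any untoward medical occurrence that results in death, is life-threatening or requires hospitalisation". The second is the remainder: "Non-serious adverse events will be defined as any other untoward medical occurrence". A third sentence deals with attribution only: "Adverse events will be classified as treatment-related if they are definitely or probably related to the exercise training intervention".

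The Feasibility section lists a safety domain with two items: "safety ((1) number of adverse events, (2) severity of adverse events"). It gives no severity scale and does not tie severity to seriousness.

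On the role of safety, the summary box after the Abstract says that the trial "will be the first to examine the safety and efficacy of a progressive interval running programme". The Exercise training section foresees that some participants may need to go back a stage, "if deemed necessary (eg, significantly increased LBP, other injuries/soreness, following periods of poor adherence").

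**The concern.** The serious class is a closed list of three outcomes, and disability is not among them. The residual sentence then settles the status of every event outside the list. Participants are aged 18 to 45 and screened for exercise risk, so death and life threat are the less likely forms of harm. A spinal or lower-limb injury with lasting loss of function is a more plausible serious harm of a running programme in this population, and it need not involve admission. Whether someone is admitted also depends on how care is delivered, so admission is an imperfect marker of lasting harm.

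What is at stake is the wording of the safety result. A report that followed the rule exactly could state that there were no serious adverse events although a participant had been left with a significant functional deficit.

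**Working it through.** No arithmetic applies. The claim concerns a classification rule and does not depend on alpha, power, an effect size or a rate. The check is to read the rule as written and look for anything elsewhere that changes it.

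1. *Is the list open or closed?* The serious class has three criteria: death, life threat and a need for hospitalisation. The article gives them as the definition, not as examples.

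2. *What happens to events outside the list?* The residual sentence makes them non-serious. Every event therefore falls in exactly one class, with no room for judgement between them.

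3. *Does another sentence add a criterion?* The relatedness sentence concerns cause, not seriousness. The safety items under Feasibility are number and severity, and neither changes the class. The Monitoring section says that there is no data monitoring committee and no independent auditing, and says nothing about classification. No other section of the article defines seriousness.

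4. *Apply the rule to test cases.*

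| Event | Fatal | Life-threatening | Requires admission | Class under the rule |
|---|---|---|---|---|
| Short-lived muscle soreness | no | no | no | non-serious |
| Injury with lasting, significant loss of function, outpatient care | no | no | no | non-serious |
| The same injury, admitted | no | no | yes | serious |

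The second and third rows describe the same harm. Only the place of care differs, and that alone changes the class. The first two rows differ greatly in harm and share a class.

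5. *What is not affected?* The second-row event is still an adverse event. It enters the count, and its severity is to be documented under Feasibility. It is misclassified, not lost.

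**The case against.** The strongest reply is that little is hidden, and much of it stands.

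- **Severity is recorded separately.** A reader might infer that the serious/non-serious split is the only grading the safety result would carry, so that a disabling injury could not be told apart from soreness. The article does not support that. Feasibility lists "severity of adverse events" as an item in its own right, and the scale may sit in the full protocol, which is not shown. Severity and seriousness are different attributes, however, so a severity grade does not correct the serious event count.

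- **The exclusions are not a ranking of gravity.** Eligibility excludes "symptomatic radiculopathy (diagnosed via medical professional or leg pain greater than back pain") and cauda equina symptoms. A reader might take this as the protocol's own view that such events are serious. The exclusions also follow from recruiting non-specific low back pain, and the same list excludes people without a suitable smartphone.

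- **Disability as a primary outcome is a different matter.** The Oswestry score is a questionnaire measure, not a seriousness criterion. Its collection in both arms at 6 and 12 weeks, with pain and MRI, gives functional decline another route into the data.

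- **No escalation is shown to fail.** A reader might infer that misclassified cases would miss an escalation step, or that the lack of a monitoring committee makes matters worse. The article describes no action that depends on seriousness. Participants are asked to report any adverse event at once, and the lack of a committee does not alter the class of an event.

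- **Safety is not a headline aim.** The aims in the Introduction are efficacy and feasibility. Safety appears in the summary box and as one feasibility domain. This limits the weight of the point, but the trial still undertakes to report on safety.

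The remaining reply is that a journal article condenses a longer document. That would answer an omission. Here the article states a complete definition and closes it, so a fuller document with a disability criterion would contradict the article, not supplement it.

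**Conclusion.** The point holds as a minor safety-reporting correction. Under the stated rule, an event that causes persistent or significant disability or incapacity, and is managed without admission, is reported as non-serious. This follows from the article's own two sentences and needs no outside source. That such an injury is a plausible harm of running in this population is a clinical judgement. The article supports it only so far as it anticipates increased back pain and other injuries.

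The size cannot be put as a rate. A reader might divide one event by the 20 planned runners (1/20 = 5%) and say that a true 5% would be reported as 0%. That is one hypothetical event, not an estimate, because the article gives no probability for such events. Nor does it show how often they would be managed without admission.

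A reader might also want prolonged hospital stay added. In a community sample an admission caused by an event already meets the hospitalisation criterion, so this would add almost nothing.

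The sample size, the primary outcomes and the efficacy analyses are unchanged.

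**What to change.** In the Adverse events section, extend the serious definition with: *results in persistent or significant disability or incapacity, or is otherwise judged medically important*. The residual sentence on non-serious events can then stay as it is.

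Do not make every new radiculopathy or fracture serious automatically. The eligibility wording counts leg pain that merely exceeds back pain as symptomatic radiculopathy, so an automatic rule could turn a temporary shift in pain into a serious event.

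Apply the revised definition to all recorded events in both arms, including those already logged, and record the reason for each decision, because re-coding involves after-the-fact judgement. No follow-up is planned beyond 12 weeks, so persistence can be judged only within that window; the report should say so.

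Note the amendment in the trial registry and in publications, as the Protocol amendments section provides, and notify the ethics committee. The cost is a wording change, the notifications and a review of the events already logged. The downside is that the serious event count may become slightly less favourable.

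### The serious adverse event definition has no criterion for lasting disability, so a disabling event managed without admission would be labelled non-serious

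*Protocol article*

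**What the plan says.** The Adverse events section of the protocol article sorts events in two ways.

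- **Seriousness.** A serious event is "any untoward medical occurrence that results in death, is life-threatening or requires hospitalisation". The rest fall into a residual class: "Non-serious adverse events will be defined as any other untoward medical occurrence".
- **Relatedness.** "Adverse events will be classified as treatment-related if they are definitely or probably related to the exercise training intervention". Events judged only possibly related are not named and so do not carry the label.

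On collection, the section states "Participants will be instructed to inform the research team immediately should any adverse events occur", and adds that "participants allocated to exercise training will be asked about adverse events during a fortnightly video consultation".

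The Feasibility section sets the safety measure as "safety ((1) number of adverse events, (2) severity of adverse events", without limiting it to related events. The Outcomes and data collection methods section likewise lists adverse events as a secondary outcome, unqualified. The key-points box in the Abstract calls the trial "the first to examine the safety and efficacy of a progressive interval running programme"; that sentence goes on to tie the claim to disc health.

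**The concern.** The seriousness rule is a closed list of three criteria followed by a catch-all. Nothing in it depends on how long an event lasts or how much function is lost, unless the participant is admitted or is in danger of dying. In a trial that deliberately loads the lumbar spine of people with chronic back pain, a lasting loss of function is a plausible form of important harm, and it need not involve an admission. Disability is important enough to this trial to be one of its three primary outcomes, yet it plays no part in deciding which events are serious.

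At stake is the serious-event count. In a trial of this size it will probably be very small, perhaps zero. A report of no serious adverse events would be correct under the definition and misleading to a reader if a lasting disability sat among the non-serious events. The Monitoring section provides for no data monitoring committee and no independent auditing, so the article describes no independent look that would pick such an event out.

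A smaller question concerns relatedness. The definite-or-probable cut-off leaves possibly related events outside the treatment-related sub-count, and a flare of back pain after a run may be hard to attribute.

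**Working it through.** No statistical calculation applies: the article gives no adverse event rate, no flare rate and no split by relatedness. The check is to run hypothetical events through the stated rules.

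**Step 1: seriousness.** The inputs are the three criteria and the residual class in the Adverse events section.

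| Hypothetical event | Death | Life-threatening | Hospitalisation | Resulting label |
|---|---|---|---|---|
| Worsened back pain leading to admission | no | no | yes | serious |
| Lasting neurological deficit, managed without admission | no | no | no | non-serious |
| Muscle soreness that settles in days | no | no | no | non-serious |

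The second and third events receive the same label. This follows from the text as written. It is not a detail left open for a fuller document, because the residual class expressly takes in whatever the three criteria do not.

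**Step 2: does another stated measure restore the distinction?**

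- *The all-event count* (Feasibility section) includes the disabling event, but counting it does not make it serious.
- *Severity* (same section) might separate the two, but the article gives no severity scale. If the serious/non-serious split is used as the grading, the wrong label passes into the severity measure as well. If a separate scale exists in the full protocol, severity would be recorded properly and the serious-event count would still be short.
- *The Oswestry Disability Index* (Disability section) is collected in both arms at baseline, 6 and 12 weeks. It measures function as an outcome and does not classify an individual event.

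None of these corrects the label.

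**Step 3: size.** The Sample size section plans 20 participants per group. One participant moved from non-serious to serious changes that arm's rate by 1/20 = 5 percentage points. How many would move is unknown and may be none.

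**Step 4: relatedness.** Take a flare recorded as an adverse event, and move its rating from probable to possible.

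- All-event number: unchanged, because the definitions of serious and non-serious carry no causality condition.
- Severity: unchanged.
- Treatment-related sub-count: lower by one.

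Only the sub-count responds to the cut-off. The safety measure set in the Feasibility section does not.

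**The case against.** **On seriousness.** The fair reply is that a disabling event would still be recorded, counted and given a severity, that the intervention is considered low risk, and that the definition contradicts nothing else in the article. All of that stands, and it is why this is a modest correction. It does not answer the point, which is that a stated rule gives the wrong label to one identifiable kind of event.

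**On relatedness.** A reader might infer that back-pain flares drop out of the safety result, and that the programme will therefore look safer than it is. The Exercise training section speaks of "daily fluctuations in pain intensity observed in up to 35% of individuals with CLBP", so a flare could often be rated as only possibly related, by staff who know the allocation. The documents do not support that inference:

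- Relatedness is a label placed on events already recorded. A flare reported as an adverse event stays in the all-event number and severity.
- No section says that safety will be judged on treatment-related events alone; the Feasibility section points the other way.
- Back pain is also scored without any causality judgement in both arms at baseline, 6 and 12 weeks, and fortnightly in the exercise arm. Flares between visits can be missed in the waitlist arm, but pain is not invisible to the trial.
- The fluctuation figure is used to justify self-selected repeats. It is an upper figure for individuals whose pain fluctuates daily, not a rate of adverse events or of uncertain attributions.
- The direction of any bias is not established. Active questioning is described for the exercise arm only, which would tend to raise the runners' all-event count relative to waitlist.

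A cut-off fixed in advance at definite or probable is a choice of specificity over sensitivity, and it is defensible. What remains is that the treatment-related sub-count, if read alone, would leave the possible category unseen.

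**Conclusion.** The main point holds: as worded, the definition files a persistent or significant disability managed without admission as non-serious, and no other stated measure corrects that label. It is a small but real defect in a trial that says it examines safety. Its numerical effect cannot be estimated from the article. Each affected participant is worth 5 percentage points in an arm of 20, and the number affected may be zero. The conclusion assumes only that the definition is applied literally.

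The relatedness cut-off is secondary and minor. It bears on a sub-count, not on the planned safety measure. The article gives no basis for saying that flares vanish from the safety result, that the treatment-related count is the trial's main safety statement, or that the treatment-related rate would be understated by any particular amount.

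**What to change.** In the Adverse events section, add persistent or significant disability or incapacity to the criteria for a serious adverse event. This costs one phrase. The downside is a possibly slightly higher serious-event count, which would be the more accurate one. As the trial is already recruiting, record the change by the route given in the Protocol amendments section and apply it to events already on file.

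For relatedness, keep the definite-or-probable cut-off if preferred, but tabulate events at each relatedness level, including possibly related, beside the all-event number and severity. This costs a few table rows and requires relatedness to be recorded by level, not only as yes or no.
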